## Abstract

**Background:**

Adenotonsillectomy is the most frequently performed operation in children worldwide. For decades, prophylactic antibiotics have been prescribed to limit postoperative complications. The effect of this antibiotic use has been refuted in a Cochrane Review. However, all reviewed studies were carried out in developed countries. In Tanzania, like many other developing countries with limited resources and a high burden of infectious diseases, postoperative antibiotic prescription is still very common to decrease the supposed higher postoperative morbidity. However, as a consequence of this widespread use of postoperative antibiotics, cross-resistance and risk of allergic side effects rise. Well-designed randomized controlled trials are needed to limit unnecessary antibiotic prescription and secondary antibiotic resistance.

**Aim:**

The aim of this study is to analyse the prophylactic role of postoperative antibiotics on morbidity following adenotonsillectomy in children in Tanzania.

**Design:**

The double-blinded, randomized, placebo-controlled trial was set in northern Tanzania. Participating centres are the Department of Otolaryngology at Kilimanjaro Christian Medical Centre in Moshi and the Department of Paediatric Surgery at the Arusha Lutheran Medical Centre in Arusha.

**Methods:**

Around 270 children aged 2–14 years, all scheduled for elective (adeno)tonsillectomy, will be included and assigned to receive either a standard regimen of 5 days of antibiotic prophylaxis or placebo after surgery. The primary outcomes are postoperative haemorrhage, fever and pain. Secondary outcomes are the time until normal diet is resumed, the time until normal activities are resumed and the occurrence of adverse events and microbial recolonization of the tonsillar beds.

**Discussion:**

This study will enhance an increase of proper antimicrobial prescription in Tanzanian institutions as well as other resource-limited countries where prescription of antibiotics is still very common. In addition, it might augment current knowledge about surface and core tonsillar micro-organisms and sensitivity patterns.

**Trial registration:**

Pan African Clinical Trials Registry, PACTR201905466349317. Retrospectively registered on 15 May 2019. https://pactr.samrc.ac.za/TrialDisplay.aspx?TrialID=8119

## Background

Adenotonsillectomy (ATE) is one of the most frequently performed operations in children worldwide and the most frequently performed otolaryngological operation in children. Indications for adenotonsillectomy are, amongst others, adenotonsillar hypertrophy, recurrent adenotonsillitis and obstructive sleep apnoea syndrome [1, 2]. This also applies to Tanzania, where both paediatric sleep apnoea as well as upper respiratory tract infections due to chronic adenotonsillar hypertrophy are very common problems. At Kilimanjaro Christian Medical Center (KCMC) alone, a large referral hospital in northern Tanzania, over 1000 adenotonsillectomies are performed yearly.

Different surgical techniques can be used to remove the tonsils and adenoid but, regardless of the surgical technique, the pharyngeal wall embedding the tonsillar fossa is left open for secondary wound healing at the end of the procedure. Subsequently, the wound bed is contaminated by commensal flora present in the oropharyngeal mucosa. It has been argued that, because of this, people are predisposed to inflammatory response and infection. This contributes to postoperative morbidity such as pain and the consequent need for analgesics, postoperative haemorrhage and the inability to resume a normal diet. For this reason, several studies have recommended the prophylactic use of antibiotics to reduce morbidity [2–5].

However, in a Cochrane Review published in 2012, involving 10 trials with a pooled population of 1035 patients, the use of postoperative antibiotics did not show a clinically relevant effect on the haemorrhage rates, the time to resume a normal diet, pain and consequent need for analgesics [5]. Little evidence suggested that prophylactic use of postoperative antibiotics reduced fever. With the existing set of evidence, Dhiwakar et al. advocated against the routine prescription of antibiotics to patients undergoing adenotonsillectomy. However, they did highlight the need for further trials including subgroups of patients who might be in need of selective administration [5]. None of the studies reviewed in this Cochrane Review had been conducted in resource-limited settings. Despite the lack of high-level evidence for postoperative antibiotics, in Tanzania all children receive postoperative antibiotics after adenotonsillectomy based on the assumption that there is a higher risk of postoperative morbidity due to limited resources and a higher burden of infectious diseases. On the other hand, the widespread use of (postoperative) antibiotics is not without risks. There is the individual risk of gastrointestinal and allergic side effects, ranging from vomiting, diarrhoea and rash to severe anaphylaxis. Also, there is the risk of antimicrobial resistance. While global concern for antimicrobial resistances rises, there is still a significant gap of knowledge on this topic in resource-limited settings, like Tanzania. In developing countries, amoxicillin is one of the most misused and wrongly prescribed drugs. The majority of young children suffering from acute respiratory infection symptoms are treated inappropriately with this antibiotic. Cross-sectional research from 2018, performed in Moshi, Tanzania, found that 92.3% of retailers dispensed antibiotics without prescriptions [6]. This practice disadvantages most inhabitants of these areas in particular. Cross-resistance and cost in obtaining superior antimicrobial agents become a big challenge.

Summarizing the aforementioned, the widespread use of postoperative antibiotics after (adeno)tonsillectomy in children in Tanzania may have more negative effects than benefits, if there are any benefits at all. To limit unnecessary antibiotic prescription and secondary antibiotic resistance, well-designed randomized controlled trials are needed. This randomized double-blind placebo-controlled trial studies the prophylactic effect of antibiotics on morbidity after adenotonsillectomy in children in Tanzania.

## Method

### Design

This study is a two-centre, double-blind, randomized controlled trial. Patients will be randomly allocated to receive either 50 mg/kg body weight of placebo or amoxicillin 5 days after surgery as the standard prophylaxis regime.

### Study setting

Participating centres are the Department of Otolaryngology at Kilimanjaro Christian Medical Centre (KCMC) in Moshi and the Department of Paediatric Surgery at the Arusha Lutheran Medical Centre (ALMC) in Arusha, the only settings with established ear, nose and throat (ENT) services in northern Tanzania.

### Study population

All children aged 2–14 years who will undergo an elective (adeno)tonsillectomy will be approached. Elective surgery is indicated in the case of recurrent chronic tonsillitis, as defined by five or more episodes of tonsillitis yearly for at least 2 consecutive years, or in the case of obstructive sleep apnoea due to adenotonsillar hypertrophy with inadequate response to pharmacotherapy. Inclusion will occur after written informed consent. Inclusion of patients started in January 2019.

Patients will be excluded from participation if they meet any of the following criteria:
The patient is scheduled for unilateral tonsillectomy, tonsillar biopsy or tonsillectomy for a known carcinoma.The (adeno)tonsillectomy is combined with any other type of surgery.The patient has an acute tonsillar infection or peritonsillar abscess at the time of surgery.The patient is known to have a cardiac co-morbidity, with or without current treatment or follow-up by a cardiologist.The patient has a condition which results in weakness or failure of the host defence mechanism, like leukaemia, acquired immune deficiency syndrome or current use of immunosuppressive medication.The patient has a syndromal disorder or a craniofacial malformation.The patient has a reported allergy to any antibiotic, ibuprofen or paracetamol.The patient was treated with antibiotics during or less than 1 week prior to surgery.Patients on any other concomitant medications at the point of enrolment.

### Study objective

The study objective is to compare the postoperative morbidity following elective (adeno)tonsillectomy in children treated with postoperative amoxicillin or a placebo in northern Tanzania. We hypothesize that placebo is non-inferior to amoxicillin in preventing postoperative morbidities following (adeno)tonsillectomy in children in northern Tanzania.

### Primary outcomes

The primary outcome is post-(adeno)tonsillectomy morbidity, but morbidity cannot be measured as a single parameter. Postoperative haemorrhage and infection are the most important postoperative complications contributing to post-(adeno)tonsillectomy morbidity. Post-(adeno)tonsillectomy infection is difficult to define since the tonsillar beds are left to heal by secondary intention after surgery in a bacterial, mucosal environment. Typical symptoms of surgical site infection are therefore absent. Clinically worsening pain and raised temperature are thus considered features of infection. For this reason, postoperative haemorrhage, raised temperature (fever) and pain are the primary outcomes in this research.

Postoperative haemorrhage is defined using two parameters: major if warranting re-admission, blood transfusion or return to theatre for haemostasis; and minor if any recorded postoperative blood loss (i.e. spitting of blood saliva 24 h post operation). Fever is defined as temperature greater than 38 °C on 2 consecutive postoperative days or greater than 39 °C on any postoperative day, and postoperative pain is rated using the Wong-Baker FACES® Pain Rating Score.

Temperature will be taken daily by the research nurse while admitted and thereafter by the parent/caretaker with an axillary thermometer until the 7th postoperative day.

The Wong-Baker FACES® Pain Rating Scale will be used to assess children’s pain perception postoperatively. Written permission has been granted from Wong-Baker FACES Foundation for using both the English (while in hospital) and Swahili (while at home) Wong-Baker FACES® Pain Rating Scale in this study. The consequent need for analgesics will be documented by the prescribing physician.

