### Randomization

Baseline characteristics of the subjects will be compiled at informed consent. Subjects will be randomly divided into an intervention arm and a control arm on the day of admission, with the aid of a computer-based randomization module in a 1:1 ratio. Stratified randomization is accomplished using gender, age group (2–4 years, 5–8 years and 9–14 years), residence (rural or urban) and research centre (KCMC or ALMC) as strata. Randomization is performed by the KCMC’s research pharmacist who will then prepare the medication (either the antibiotics or placebo capsules or solution, depending on the age of the child). Both the placebo capsules as well as solution have the same taste and appearance as the amoxicillin capsules and solution. Labelled with only the study protocol number and patients’ details, the medication will be distributed by one of the research nurses. Thus, all health professionals involved in the trial process will be blinded.

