### Follow-up

During discharge, a questionnaire will be provided to the persons legally responsible for the participating child. This will be filled out daily and will be presented to the investigator at follow-up visits. The questionnaire is translated, adopted and modified from the standardized Linden et al. [10] post-tonsillectomy follow-up questionnaire (Additional file 1).

On day 7, the wound bed and the general health status will be inspected by the study doctor at the Department of Otolaryngology at KCMC and ALMC respectively. On day 14, a third swab (Copan ESwab; Copan Italia SPA) of the surgical site will be taken and sent to the microbiology research laboratory for culture and sensitivity analysis, as already described. During both visits, detailed information will be obtained by the study doctor. The entire process from patient allocation to follow-up is displayed in Fig. 1 and well described in a SPIRIT (Standard Protocol Items: Recommendations for Interventional Trials) figure in Fig. 2.

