### Statistical analysis

Continuous variables will be presented as means and standard deviation or median and interquartile range (IQR) if not normally distributed. Categorical data will be presented as a number with percentage. All analysis will be done according to an intention-to-treat protocol.

Differences between the observed risks of events (for primary outcomes of bleeding and fever) between the placebo and antibiotics groups will be calculated along with their 95% confidence intervals. Absolute risks will also be presented as it is important to be aware of the underlying risk of events. Differences in pain score between the two treatment arms will be calculated as mean differences with 95% CIs, using Student’s *t* tests. Secondary outcomes will be analysed using chi-squared tests for categorical data (return to normal activities and microbial recolonization) or Wilcoxon rank-sum tests (days to return to normal diet) for continuous data. *P* < 0.05 will be considered statistically significant. All data will be coded to maximize confidentiality. Collected data will be entered into a database and analysed using IBM SPSS Statistics version 24.

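### Pain, a primary outcome, is scored from age 2 on a faces scale meant for the child's own perception, but the article names no rater and pools all ages in one unstratified comparison

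*Protocol article*

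**What the plan says.** Under Primary outcomes, the protocol article states that "postoperative haemorrhage, raised temperature (fever) and pain are the primary outcomes in this research". Worsening pain is treated there, with raised temperature, as a feature of infection. The only pain instrument named is the faces scale: "postoperative pain is rated using the Wong-Baker" FACES scale, and the "Pain Rating Scale will be used to assess children’s pain perception postoperatively". An English version is used in hospital and a Swahili version at home.

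Under Study population, "All children aged 2–14 years who will undergo an elective (adeno)tonsillectomy will be approached". Under Randomization, the strata include "age group (2–4 years, 5–8 years and 9–14 years".

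Under Follow-up, "a questionnaire will be provided to the persons legally responsible for the participating child". It is filled in daily and brought to the visits. The questionnaire itself (Additional file 1) is not at hand.

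Under Statistical analysis, "Differences in pain score between the two treatment arms will be calculated as mean differences with 95% CIs", by Student's t test. No split or adjustment by age or by rater is described, and all analyses are to follow intention to treat. The Study objective section frames the trial as non-inferiority: "We hypothesize that placebo is non-inferior to amoxicillin in preventing postoperative morbidities".

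**The concern.** The scale is meant to record the child's own perception, and it is the only pain measure across a range that starts at age 2. Whether every child in the youngest stratum can choose a face for his or her own pain is not something the plan can take for granted. The article does not say what happens when a child cannot. An adult would probably supply the score, possibly a nurse on the ward and a caretaker at home. The analysed variable could then be self-report in older children and an adult's impression in some younger ones, with the adult changing at discharge.

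This matters for two reasons. First, in a non-inferiority trial, anything that pulls the arm difference towards zero makes it easier to conclude that placebo is no worse. Second, who chose the face is settled when the score is collected. If it is not recorded then, no later analysis can separate the two kinds of score.

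**Working it through.** **The plan's own figure.** The only worked sample size concerns haemorrhage. Inputs from Study sample: event rate 2.5% in both arms, margin 5%, α 0.05, power 0.80. Taking α as one-sided:

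n per arm = (1.645 + 0.842)² × 2 × 0.025 × 0.975 / 0.05² = 6.18 × 19.5 = 120.6, so 121 per arm and 242 in total.

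This matches the article. With one-sided 0.025 the same formula gives 154, which does not match. The figure says nothing about pain: the article gives no SD, margin or assumed difference for it.

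**Who assesses what, as stated in the article.**

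| Measure | In hospital | At home |
|---|---|---|
| Temperature | research nurse | parent or caretaker |
| Need for analgesics | prescribing physician | prescribing physician (no separate home rule) |
| Pain (faces scale) | English version, rater not named | Swahili version, rater not named; adult holds the questionnaire |

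**How far mixed ratings could move the mean difference.** Let f be the share of children with proxy scores and r the share of the true difference Δ that those scores carry. Then

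observed difference = Δ × [1 − f(1 − r)].

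The article gives no age distribution. As an assumption, take ages uniform over the 13 years from 2 to 14: age 2 alone is 1/13 (about 21 of 270) and ages 2–4 are 3/13 (about 62 of 270). For Δ = 1.0 point:

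| Proxy share f | r = 0 | r = 0.5 | r = 0.8 |
|---|---|---|---|
| 1/13 (age 2 only) | 0.92 | 0.96 | 0.98 |
| 3/13 (whole 2–4 stratum) | 0.77 | 0.88 | 0.95 |

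A younger case mix would raise f. The r = 0 column is a worst case.

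**The same in power terms.** Assume a true standardized difference of 0.36, which gives 80% power at 121 per arm with two-sided 0.05. Power = Φ(d√(121/2) − 1.96), with d = 0.36 × [1 − f(1 − r)]:

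| f | r = 0 | r = 0.5 | r = 0.8 |
|---|---|---|---|
| 0.1 | 71% | 76% | 78% |
| 0.2 | 61% | 71% | 77% |
| 0.3 | 50% | 66% | 75% |
| 0.4 | 39% | 61% | 73% |

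This is the chance of seeing a real difference, so the loss runs from about 2 to about 41 percentage points.

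**If proxies only add noise.** With extra variance v (as a multiple of the ordinary variance) in the share f, the mean difference stays unbiased and the SD grows by √(1 + fv). From f = 0.1, v = 0.25 to f = 0.4, v = 1.0, the factor runs from 1.01 to 1.18 and power from 79% to 66%. In a non-inferiority comparison the wider interval works against the placebo claim.

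**What stratifying does and does not do.** If the 2–4 stratum carried no signal, combining stratum estimates by size would still give 10/13 = 0.77 of the true difference. Stratifying takes differences in pain level between age groups out of the error and shows where the estimate comes from. It does not undo attenuation, so the separate 2–4 result and the self-report sensitivity analysis are needed as well.

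**The case against.** The strongest objection is that the article never says proxy ratings are used. An adult who holds the questionnaire may simply record the face the child points to. The rule may also sit in Additional file 1 or the full protocol, and an article may leave such detail there. This stands in part: a reader might infer that self-reports and proxy scores are in fact pooled and that the arm difference is in fact diluted, and the text supports neither. The omission is still worth raising. The same section does name assessors for temperature and analgesic need, and the pooled, unstratified t test is stated outright.

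It can also be said that the article gives no lower age limit for the scale, and that the 2–4 band is a randomization stratum, not a property of the instrument. That is right. The cut at 5 years used below is a practical one, taken from the existing strata.

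Blinding and age-stratified randomization should balance young children and their raters between arms. That also stands: the issue is attenuation or precision, not imbalance between arms.

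Finally, a reader might take the Discussion's remark that young age is likely to worsen outcomes to mean that the antibiotic effect is largest in the youngest. The remark concerns prognosis and says nothing about the size of the treatment effect.

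**Conclusion.** The point holds as a gap in how a primary outcome is measured and analysed. One faces scale for the child's own perception is used from age 2, no rater is named for pain, and all ages enter one unstratified comparison. Mixing of self-report and proxy scores is a possibility, not an established fact. If it occurs, the effect depends on how proxies behave: attenuation would favour non-inferiority, while pure noise would count against it.

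The size cannot be derived from the article, because the age mix, the share of proxy scores, their agreement with self-report, and the SD and margin for pain are not given. Under the assumed uniform ages, the observed share of a true difference lies between 0.77 (whole 2–4 stratum, no signal) and 0.98 (age 2 only, 80% signal). No stated figure in the protocol changes, since the sample size rests on haemorrhage.

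**What to change.** In data collection:
- State who chooses the face for each age group and setting, including what is done when a child cannot choose.
- For the 2–4 year stratum, keep that rater the same on the ward and at home.
- Record the rater with every score.

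In the analysis:
- Keep all randomized children in the primary pain comparison, in line with the intention-to-treat statement. Restricting that comparison to age 5 and over would drop randomized children.
- Estimate the mean difference with its 95% CI, adjusted for or stratified by the randomization age groups.
- Report the 2–4 year stratum separately.
- Add a sensitivity analysis limited to self-reported scores (age 5 and over).

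The cost is one form field and a little more analysis. The sensitivity estimate is less precise: under uniform ages it loses 3/13, or about 23%, of children (242 × 10/13 ≈ 186), so its interval is about √(13/10) = 1.14 times as wide at equal SD. Recruitment has already begun, so the rater can be recorded only from the change onward unless the existing form captures it. The age-group analysis can use every child already enrolled.

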### Secondary outcomes

The secondary outcomes include the time until normal diet is resumed, time until normal activities are resumed and occurrence of adverse events (rash, vomiting, diarrhoea and anaphylaxis) and microbial recolonization of the tonsillar niche.

### Study sample

Postoperative bleeding, fever and pain were used as primary outcomes. We calculated power for all primary outcomes and only took the outcome with the largest number of participants. Based on the latest Cochrane Review, titled “Antibiotics to reduce post-tonsillectomy morbidity” [5], 2.5% of all patients who undergo an elective tonsillectomy have a significant postoperative haemorrhage. With this haemorrhage rate, a significance level (α) of 0.05, a power (π) of 0.80 and a non-inferiority margin of 5%, we calculated the number of patients in our intervention group. The group treated with antibiotics should include 121 patients, giving a total of 242 patients necessary for analysis. To allow for some loss to follow-up, the aim is to include 270 children.

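### The 121 per arm fits only a one-sided 5% test, while the analysis plans 95% intervals; if the 95% limit decides, power for haemorrhage is about 70%, not 80%

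*Protocol article*

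**What the plan says.** The Study objective section of the protocol article frames the trial as non-inferiority: "We hypothesize that placebo is non-inferior to amoxicillin in preventing postoperative morbidities". The Study sample section says that power was calculated for each primary outcome and the largest requirement kept. It then gives only the haemorrhage calculation, starting from a rate taken from a systematic review: "2.5% of all patients who undergo an elective tonsillectomy have a significant postoperative haemorrhage". The other inputs follow in one sentence: "With this haemorrhage rate, a significance level (α) of 0.05, a power (π) of 0.80 and a non-inferiority margin of 5" per cent. The result is: "The group treated with antibiotics should include 121 patients, giving a total of 242 patients necessary for analysis". Enrolment is set at 270 to allow for loss.

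The Statistical analysis section says that risk differences for bleeding and fever "between the placebo and antibiotics groups will be calculated along with their 95% confidence intervals", with P below 0.05 as the general threshold for significance. It mentions no one-sided test and no 90% interval, and it does not say which limit is compared with the margin.

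**The concern.** A non-inferiority sample size depends directly on whether alpha is one-sided or two-sided. Comparing the upper limit of a two-sided 95% interval with a margin is a one-sided 2.5% test. Doing the same with a 90% interval is a one-sided 5% test. If the size was worked out at one level and the result is judged at the other, the stated power does not describe the planned analysis.

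Haemorrhage is a primary outcome, and by the article's own account it is the one that fixed the trial's size. The trial is meant to inform whether routine antibiotics can be dropped, so an inconclusive haemorrhage result would be costly. Understating how likely that is gives readers and the monitoring committee a wrong expectation. While the level is open, the 90% or the 95% limit could also be chosen after the data are known, and with few events that choice could change the conclusion.

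**Working it through.** **Inputs.** Haemorrhage rate p = 0.025, margin d = 0.05 absolute, alpha 0.05 (side not given), power 0.80 and 121 per arm, all from Study sample; 1:1 allocation from Randomization; 95% intervals from Statistical analysis. An equal true rate in both arms is an assumption, and it is the one under which the plan's figure reproduces.

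**Reproducing 121.** Normal approximation, per arm:

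n = (z_alpha + z_beta)² × 2p(1 − p) / d²

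Here 2p(1 − p)/d² = 2 × 0.025 × 0.975 / 0.0025 = 19.5.

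- One-sided 5%: (1.645 + 0.842)² × 19.5 = 120.6, so **121** per arm and 242 in total, as in the article.
- One-sided 2.5%: (1.960 + 0.842)² × 19.5 = 153.05, so **154** per arm and 308 in total.
- Equivalence with 5% per side: 167 per arm.
- Superiority, 2.5% against 7.5%: 234 (one-sided) or 298 (two-sided) per arm, and 273 or 336 with continuity correction.

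Only the first variant matches.

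**Power with the planned 95% interval.** Power = Phi(d/SE − 1.960), with SE = √(2 × 0.025 × 0.975 / n).

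- n = 121: SE = 0.02007, d/SE = 2.491, Phi(0.531) = **70.2%**.
- n = 135 (all 270 analysed): SE = 0.01900, d/SE = 2.631, Phi(0.671) = **74.9%**.
- n = 154: 80.2%.

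With 1.645 in place of 1.960, n = 121 gives Phi(0.846) = 80.1%, the article's own power.

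**Dependence on the interval method.** The expected number of events is 121 × 0.025, about 3 per arm, so the normal approximation is rough. Exact binomial enumeration at 2.5% in both arms gives this probability that the upper limit falls below 5 points:

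| Per arm | Interval | Wald | Newcombe | Score (Farrington-Manning) |
|---|---|---|---|---|
| 121 | 95% | 70.3% | 54.6% | 54.1% |
| 121 | 90% | 82.2% | 72.2% | 72.2% |
| 135 | 95% | 76.4% | 62.6% | 58.2% |
| 135 | 90% | 84.7% | 74.5% | 74.5% |
| 154 | 95% | 80.6% | 67.6% | 67.6% |

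The 70% therefore belongs to a Wald limit. A score or Newcombe limit gives clearly less at the same size.

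**The case against.** The strongest reply is that both ends of the mismatch are inferred. The article does not say that alpha is one-sided; that comes from back-calculation. Nor does it say that the upper 95% limit decides non-inferiority. Reporting a 95% interval does not rule out a one-sided 5% test as the formal comparison, and that would keep 80.1% power at 121 per arm. A one-sided 5% level is a legitimate choice, and a decision rule may stand in an analysis plan that is not shown. All of this is correct, so a reader who concludes outright that the trial has 70% power, or that 121 is a miscalculation, goes further than the text allows: 121 is right for one-sided 5%, and 70% is conditional on the 95% limit deciding.

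What remains is not an omission. The article states a power and states an interval, and the two do not belong together on the natural reading. The 95% interval is the only inferential tool it gives for comparing bleeding between the arms.

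A reader might also infer that the planned interval has a poor error rate because a Wald limit performs badly with so few events. The article names no interval method for the analysis, so that would criticise a choice it has not made.

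It can also be said that enrolling 270 covers the gap. It does so only in part: with no loss at all, power by the formula is about 75%, and the Study limitations section itself warns that loss may exceed the estimate.

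**Conclusion.** The point holds in conditional form. The sample size corresponds to one-sided 5%. If non-inferiority for haemorrhage is judged on the upper limit of the planned 95% interval, power is about 70% with 242 analysed and about 75% with 270. The chance of missing non-inferiority when the true rates are equal is then about 30% rather than 20% at the planned analysis size, and about 45% with a score or Newcombe limit.

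These figures assume a true rate of 2.5% in both arms, and the 70% and 75% also assume a Wald-type limit. The 2.5% refers to significant haemorrhage, whereas the Primary outcomes section also defines minor bleeding, so none of these figures gives the power for a definition that includes minor bleeds.

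The calculation does not show that more children must be recruited. The 154 per arm is what 80% would take at the 95% limit under the formula used; it measures the gap and is not a demand.

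**What to change.** In Study sample, state the side of alpha and make it agree with Statistical analysis, before anyone on the trial team sees results by arm. Two routes are open:

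- **(a)** Keep the 95% interval, say that its upper limit is compared with the 5-point margin (one-sided 2.5%), and restate the power.
- **(b)** State that haemorrhage non-inferiority is judged at one-sided 5% on the 90% interval, and say so in Statistical analysis as well.

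In either case name the interval method and quote the power that goes with it. At 121 per arm:

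- Wald limit: about 70% under (a); about 80% under (b) by the formula, or 82% by exact enumeration.
- Score or Newcombe limit: about 54–55% under (a); about 72% under (b).

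The 70% figure should not be paired with a score limit.

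The cost is a few sentences in two sections and, except under (b) with a Wald limit, a less favourable stated power. No extra patients are needed.
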